### 2.2. Eligibility Criteria

Subjects aged 3 to 12 years diagnosed with PFF. For the diagnosis of the PFF, the following criteria must be met:Foot Posture Index (FPI) > 6 [33].Navicular drop > 10 mm [34].Relaxed calcaneal stance position (RCSP) 6° to 12° valgus [35].Pronation angle > 10° [36].Arch index > a 1.35 [37].Double/single heel rise test negative [38].Windlass test negative [39].

In addition, the signature of the parents or legal guardians with consent to participate in the study will be necessary (Appendix B).

Participants will be excluded if they have undergone any surgery in the lower limbs, have previously received treatment for PFF, present osteoarticular injury, foot fractures or in the lower limbs in the last 6 months, ankle sprain, asymmetry, systemic diseases with osteoarticular involvement that present symptoms in the lower limb with gait disturbance (for example, Perthes disease) or biomechanical alteration of the lower limb with repercussions on the foot and ankle. Children suffering from any type of neurological or systemic disability (cerebral palsy, Down Syndrome, clubfoot or equino-varus, …) will also be excluded.

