### 2.4. Outcomes Measures

The document presented in Appendix C will be used for data collection. It contains all the data to be collected in the anamnesis and all the variables to be studied, including all the clinical tests that would be carried out.

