
#### 2.4.2. Quantitative or Numerical Variables

Age: in months.Weight: in Kg.Height: in meters.Body Mass Index (BMI): Will be calculated with the formula weight (Kg) divided by height squared (meters^2^). The classification of each child in low weight, normal weight, overweight or obesity will depend on the child’s sex, height, weight and age [44].Pain: visual analog scale (from 1 to 10, 1 being minimum pain and 10 maximum pain).FPI: The six clinical criteria used in PFI are: 1. palpation of the talus head; 2. curvature supra and lateral inframaleolar region; 3. position of the calcaneus in the frontal plane; 4. prominence of the talonavicular region; 5. congruence of the internal longitudinal arch and 6. abduction/adduction of the forefoot with respect to the rearfoot. (Score: neutral = 0; clear signs of supination = −2; clear signs of pronation = +2) [33].RCSP: degrees of calcaneal eversion. The valgus degrees of the calcaneus are measured in bipedal support [35].Navicular drop: in millimeters. It measures the difference between the navicular position when the patient’s foot is in a neutral position and when the patient’s foot is in its normal position. It measures how many millimeters the medial tuberosity of the scaphoid has descended [34].Pronation angle: in degrees. To calculate the bisection of the distal third of the tibia with respect to the bisection of the calcaneus [36].Chippaux-Smirak index: in cm. On the footprint of the subject taken from a pedigraphy, the narrowest distance from the medial part of the foot (B) with the widest distance from the forefoot (A) must be measured. It is divided B/A [45].Pressure platform: percentage of load/weight on each foot and distribution of the same (anterior load, posterior load, load of the left and right foot) [43].Arch index: numerical scale. The patient’s footprint is taken with a pedigraphy, the toe area is excluded and a longitudinal line is drawn that goes from the center of the heel to the 2nd toe. A line is then drawn perpendicular to the 1st. Two lines are drawn perpendicular to this axis to see the anterior extent of the forefoot area. The axis of the foot is divided into 3 equal parts and here 3 zones are defined: A: forefoot, B: midfoot and C: rearfoot. The arch index is calculated: B/(A + B + C) [37].Foot size: in cm.Silfverskiold test: in degrees. The degrees of dorsiflexion of the ankle (starting from a position of 90°) with extended knee and bent knee [46] will be measured.Navicular height: in millimeters. Measure the height of the scaphoid to the ground with the subject sitting [47].

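### Navicular drop and height are set in raw millimetres for ages 3 to 12 while the listed foot size has no role: avoidable noise if follow-up values are compared directly, and growth drift in within-group change

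*Protocol article*

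**What the plan says.** All places are in the protocol article.

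- **Population (2.2):** "Subjects aged 3 to 12 years diagnosed with PFF". One entry threshold, "Navicular drop > 10 mm", applies at every age.
- **Navicular measures (2.4.2):** "Navicular drop: in millimeters. It measures the difference between the navicular position" in the neutral and the habitual stance; and "Navicular height: in millimeters. Measure the height of the scaphoid to the ground with the subject sitting". Neither is scaled.
- **Footprint measures (2.4.2):** by their formulas these are ratios. The Chippaux-Smirak index is B/A, and the arch index is B over the sum of A, B and C.
- **Foot size (2.4.2):** "Foot size: in cm". No use in scaling or adjustment is given.
- **Data form (2.4):** of the Appendix C form the article says "It contains all the data to be collected in the anamnesis and all the variables to be studied". Table A2 in that appendix has no field labelled foot size; it has an unexplained entry, Standing number.
- **Analysis (2.7):** groups are compared by Student's t or ANOVA, or by rank tests, within a bivariate analysis. Regression appears only for relating quantitative variables to each other. No covariate is named, and the section does not say whether follow-up values or changes are compared.
- **Expectation (Abstract):** foot biomechanics should improve on the initial measurements in both arms. Section 2.5 repeats the measurements up to 12 months.

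**The concern.** A small and a large foot with the same arch shape score differently in millimetres. Over a nine-year age span, that difference sits in the error term of an unadjusted comparison and costs power on two measures that bear closely on arch collapse.

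Children also grow between visits. If shape stays the same, navicular height and navicular drop both rise. A higher navicular reads as a better arch and a larger drop as a worse one, so growth alone would make the two measures point in opposite directions when follow-up is compared with baseline. The Introduction itself cites natural development of the foot as the rival explanation for change.

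The article lists the variable that would deal with this but gives it no job, and the data form does not clearly record it.

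**Working it through.** **1. The article's own figure.** Section 2.6 states 64 per group for 80% power at 0.05, with a clinical variation of 2 and an SD of 1. With n = 2(1.96 + 0.84)²/d² = 15.70/d²:

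- d = 2/1 = 2 gives 15.70/4 = 3.9, so 4 per group.
- d = 1/2 = 0.5 gives 15.70/0.25 = 62.8, so 63 per group, or 64 with the t distribution.

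The stated 64 therefore matches d = 0.5, not the stated inputs. That is a separate matter. Here d = 0.5 at 64 per group serves only as a reference with 80% power.

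**2. Share of variance due to foot size.** This step is assumed, since the documents give no foot lengths, means or SDs. Take foot length uniform over 16–24 cm and millimetre values proportional to it. The coefficient of variation (CV) of foot length is (8/√12)/20 = 0.115. With mean m and size-free SD s, R² = (m·CV)² / [(m·CV)² + s²].

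| Measure | m (mm) | (m·CV)² | s (mm) | R² |
|---|---|---|---|---|
| Height | 30 | 12.0 | 4 to 8 | 12.0/28.0 = 0.43 to 12.0/76.0 = 0.16 |
| Drop | 12 | 1.92 | 2 to 4 | 1.92/5.92 = 0.32 to 1.92/17.92 = 0.11 |

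A second set of assumptions (foot size rising linearly from 15–16 cm at age 3 to 22–24 cm at age 12, size-free CV 15–30%) gives R² of 0.12 to 0.46 for height.

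**3. Power of an unadjusted t test on follow-up millimetres.** The effective d is 0.5·√(1 − R²), with 64 per group, two-sided 5%.

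| R² | d | Power |
|---|---|---|
| 0 | 0.50 | 80% |
| 0.12 | 0.47 | 75% |
| 0.20 | 0.45 | 71% |
| 0.30 | 0.42 | 65% |
| 0.46 | 0.37 | 54% |

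For height the range is roughly 55–75%. For drop, the entry rule of more than 10 mm cuts off the lower tail and changes the link with foot size. With that rule simulated, the loss ranged from about 1 to 18 percentage points, depending on the inputs.

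**4. Does use of the baseline value help?** Simulation with 3,000 runs, 64 per group, size-free d = 0.5, mean 12 mm and SD 3 mm for drop, mean 30 mm and SD 6 mm for height, and correlation of the size-free part between visits of 0.5 and 0.7:

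| Analysis | Power |
|---|---|
| Follow-up mm, unadjusted | 71–73% (drop), 68% (height) |
| Follow-up mm, adjusted for foot size | 79–80% |
| Change in mm | 80–95% |
| ANCOVA on baseline mm | 87–97% |
| The same ANCOVA plus foot size | 88–97% |

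With no true effect, the rejection rate was 4.7–5.8% throughout.

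**5. Growth with shape unchanged (assumed).** Growth of 3–6% a year adds 25 × 0.03 to 25 × 0.06 = 0.75–1.5 mm to a height of 25 mm, and 12 × 0.03 to 12 × 0.06 = 0.36–0.72 mm to a drop of 12 mm. Growth of 0.5–1.5 cm on a 20 cm foot (2.5–7.5%) adds 0.75–2.25 mm to a height of 30 mm and 0.3–0.9 mm to a drop of 12 mm. The shift is the same on average in both arms. It cancels between arms but not within them.

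**The case against.** The strongest reply is that section 2.4.2 states units of measurement, not the analysed variable. Section 2.7 does not fix follow-up values over change, and a condensed article may leave covariates to a fuller plan. If baseline is used, almost nothing is lost: foot size adds only about 0–1 point to a baseline ANCOVA. This stands, and it makes the power loss a conditional worst case.

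Dividing drop by foot size may also gain little. Entry at a fixed millimetre threshold admits small feet only if their relative drop is high. In a simulation with that rule, where mean drop before selection was 4.5–5% of foot size, foot size explained 7–15% of the variance of drop in mm but 12–22% of that of the ratio, and the CVs were nearly equal. This also stands, and is why the covariate form is named first for the between-arm analysis.

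Scaling does not make within-group change a treatment effect either, since the article cites arch formation up to age 10. It removes the size component only.

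Four stronger readings are tempting but not supported:

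- **The arm comparison is biased.** Randomisation balances foot size and growth on average, and the error rate stayed near 5%.
- **The trial is underpowered for this reason.** Neither measure is named primary, and section 2.6 does not name the outcome behind its calculation.
- **Foot size will not be collected.** Section 2.4.2 lists it, and Standing number may be a translated foot or shoe size. The form is unclear, which is a smaller fault.
- **The entry threshold must change.** Nothing here requires that.

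**Conclusion.** The point holds in a limited form, as a cheap improvement to two measures that are not named as primary. What rests on the text alone: both are in raw millimetres over ages 3 to 12, foot size is listed without a role, the named group tests are unadjusted, and the form has no clear foot-size field.

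The size of the loss rests on assumed foot lengths, means, SDs and proportional scaling. If follow-up values are compared directly, 80% power becomes roughly 55–75% for height, and drop loses less, by an amount that depends on the inputs. With baseline-adjusted or change analyses the loss nearly disappears.

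Growth drift in within-group change is not removed by using baseline. Under the assumptions above it is about 0.75–2.25 mm for height and 0.3–0.9 mm for drop. It matters because the abstract expects both arms to improve on baseline.

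**What to change.** 1. In 2.7, compare navicular drop and height between arms with the baseline value and foot size as covariates. Analysing per cent of same-visit foot size is an alternative, with the caution above for drop.
2. In 2.4.2, report within-group change as per cent of same-visit foot size, and keep the millimetre values as description.
3. In Table A2, add Foot size (cm), recorded at every visit, and explain or remove Standing number. This must be settled before data collection, because a foot size not measured at a visit cannot be recovered later.

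The cost is a sentence in each of two sections and one form field. Per cent values are less comparable with reports in millimetres, hence keeping both, and error in measuring foot size adds slight noise. The entry criterion is untouched.

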## Appendix C. Patient Medical History and Report

**Table A2 jpm-13-01269-t0A2:** Patient Medical History and Report.

ANAMNESIS.		
Name:		Identification Code:
Name and ID father/mother/legal guardian:		
Address:		Phone:
DNI:	Email:	
Date of birth:		Age:
Weight:	Height:	BMI:
Allergies:	Background:	
Standing number:	Gender: Male/Female	
Level of physical activity:	High/Medium/Low	
Exploration-Assessment		
IPF	Punctuation:	Pronated/Normal/Supinate
Navicular Drop	(mm)	
Double Heel Rise Test	Positive/Negative	
Single Heel Rise Test	Positive/Negative	
Pain (VAS scale)	Symptomatic/Asymptomatic	Punctuation:
PRCA	(degrees)	
Windlass Test	Positive/Negative	
Arc height index	Punctuation:	
Maximum pronation test	Positive/Negative	
ASA axis	Lateralized/Neutral/Medialized	
Supination resistance test	High/Moderate/Low	
Chippaux-Smirak Index	(cm)	
Beighton scale	Punctuation:	Hyperlax/Normal
Type of forefoot	Abduccido/Neutral/Adducido	
Footwear	Heel level: Medial/Center/Lateral	
Podoscope	Pronate/Supine/Neutral	
Pronation Angle	(degrees)	
Silfverskiold Test	(degrees)	
Navicular height	(mm)	
Pressure platform		
Maximum pressure zone:		
Center of gravity		
Gait progression line		
Load/weight percentage	Left	Right
	Ant: Post:	Ant: Post:
	Left:	Dx:

**
REPORT EXERCISES AND RECOMMENDATIONS
**

Exercises to be performed:

1. Tiptoe for 1 min.
2. Walk with the outer lateral edge of the foot for 1 min.
3. Stand on tiptoe, hold on for 2 s and go down 15 times.
4. Hold a tennis ball with your heels and stand on tiptoe without the ball falling, hold 2 s and go down. Perform 15 repetitions.
5. Take marbles or pens with your toes and try to put them in a bucket or change them for 1 min.
6. Stand on a towel or paper and crumple it with your toes, make this gesture for a minute.
7. Standing try to increase the arch of the foot making the greatest possible effort, do 15 repetitions.
8. To finish, standing with a ball under the sole of the foot make pressures at different points of the foot and perform stretching of the triceps sural with extended knee and bent knee.

All exercises will be repeated twice each.

All these exercises will not structure the deformity and do not develop compensations in other body segments. With them we are working all the intrinsic and extrinsic muscles of the foot involved in children’s flatfoot. The rebalancing of this musculature will cause the stabilizing function of the foot to develop, in addition to improving its correct activation during dynamics.

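### Section 2.4.2 and the Appendix C data form are inconsistent on three entries: the Chippaux-Smirak unit, the arch measure and the Silfverskiold knee positions

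*Protocol article*

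**What the plan says.** Section 2.4 of the protocol article ties the outcomes to the printed form: "The document presented in Appendix C will be used for data collection", and "It contains all the data to be collected in the anamnesis and all the variables to be studied". Three variables then read as follows.

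- **Chippaux-Smirak index.** Section 2.4.2 opens the entry with "Chippaux-Smirak index: in cm". It goes on to say that "the narrowest distance from the medial part of the foot (B) with the widest distance from the forefoot (A) must be measured", and then "It is divided B/A". Table A2 in Appendix C has one row for the index, marked cm, with no separate places for A and B.
- **Arch index.** Section 2.4.2 splits the footprint, without the toes, into three zones and states: "The arch index is calculated: B/(A + B + C"). Table A2 has no row of that name. It has "Arc height index", with a score. Section 2.2 uses an arch index above 1.35 as an entry criterion.
- **Silfverskiold test.** Section 2.4.2 asks for ankle dorsiflexion in degrees "with extended knee and bent knee". Table A2 has one row in degrees and does not mention knee position.

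**The concern.** The form is what staff fill in, and the article says it is complete. Where it disagrees with the definitions, or copies an internal contradiction from them, two assessors can write different things in the same field and both claim to have followed the plan. Taken literally, the form could produce a length in place of a ratio, an arch measure other than the defined one, or an angle with no known knee position.

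Section 2.5 schedules four assessments, and section 2.1 recruits from two universities and nearby schools, so inconsistent filling-in is a practical possibility. Two stated aims are the most exposed. The abstract expects both arms to improve on their initial measurements, which is a within-group comparison. The Introduction and section 3 plan to correlate clinical methods with the diagnosis and severity of flat foot. The arch index matters further because it is also used for entry.

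**Working it through.** The plan gives no figure to reproduce on this point. The check sets the entries side by side, with one unit check, one bound and one scale illustration.

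**1. Chippaux-Smirak: unit.** By section 2.4.2 the index is B/A, with A and B both footprint widths. The unit is cm / cm, so there is none. The unit cm and the formula B/A therefore cannot both describe the recorded value. The contradiction lies inside section 2.4.2, and Table A2 carries it over; text and form agree with each other on cm.

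*What would follow if a width were entered.* Assume B = 3.5 cm, A = 7.0 cm and growth in proportion by a factor g. These are assumptions; the documents give no such figures.

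| Growth | B × g (cm) | A × g (cm) | B/A |
|---|---|---|---|
| 0% | 3.50 | 7.00 | 0.50 |
| 4% | 3.64 | 7.28 | 0.50 |
| 6% | 3.71 | 7.42 | 0.50 |
| 8% | 3.78 | 7.56 | 0.50 |

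The factor g cancels in B/A. A midfoot width rises by 0.14 to 0.28 cm with no change in arch shape. This applies only if someone enters B instead of B/A.

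**2. Arch index: name and range.** Section 2.4.2 defines B/(A + B + C). The form names an arch height index, which the article defines nowhere. The three zones are parts of one footprint, so A and C are not negative and B/(A + B + C) ≤ 1. The entry threshold would need B = 1.35 × (A + B + C), that is −0.35 × B = 1.35 × (A + C). The left side is negative for any B > 0 and the right side cannot be, so no footprint satisfies it. The arch measure thus has one definition in 2.4.2, a threshold in 2.2 that this definition cannot reach, and a different name on the form.

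**3. Silfverskiold: fields.** Section 2.4.2 requires two knee positions. The form gives one row in degrees. Elsewhere the same form does separate paired results: double and single heel rise have their own rows, and platform load is split by side and by front and back. Two numbers could be written in the Silfverskiold row, but nothing on the form says which is which, and a lone number cannot be assigned to a position later.

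**The case against.** The strongest reply is that section 2.4.2 already says what to do. Both widths must be measured, the division is written out, and both knee positions are required. Staff who follow the text get the right quantities. B/A and the arch index can be recomputed from the pedigraph prints if these are kept. Table A2 is full of half-translated labels, no arch height index is used anywhere else, and navicular height already has its own row, so the odd arch label may be a translation slip. The row layout was also read from a PDF, and a journal article may leave detailed form design to the full protocol.

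Much of this stands. A reader might infer that the three outcomes cannot be obtained from the form. The documents do not support that: a ratio can be written in the Chippaux-Smirak row despite the printed unit, two angles fit in one row, and footprints can be re-read. A reader might also infer that the index will show a false worsening as the children grow. That needs a width to be entered against the written instruction to divide, and the growth figures are assumed. It would also be expected in both randomised arms alike, so it would add noise and distort within-arm change rather than bias the comparison between arms.

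The reply does not remove the inconsistencies. The article prints its form and calls it complete, so these are conflicts in stated text and not omitted detail. A translation slip in a field name still has to be corrected before the field is used. It also cannot explain the 1.35 threshold, which conflicts with the definition in 2.4.2 whatever the form says.

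**Conclusion.** The three inconsistencies are real and the plan is wrong as written on each: a unit given to a unitless ratio, a defined arch index with no row of its name and an entry threshold it cannot reach, and two required knee positions sharing one unlabelled row. The consequence is a risk of ambiguous or inconsistent recording across four assessments, mainly for within-group change and the correlation analyses. It is not a demonstrated loss of data or a bias in the treatment comparison.

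Severity is minor. Three of many outcomes are affected, none is named as primary, and no sample size figure depends on them. The unit check and the bound on B/(A + B + C) need no assumption beyond the definitions in section 2.4.2. The growth illustration rests on assumed widths and growth and is conditional on a recording error.

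**What to change.** 1. **Chippaux-Smirak.** Delete cm in section 2.4.2 and in Table A2. Record B/A, or B/A × 100 as a percentage. Ideally add fields for widths A and B so that the ratio can be checked.
2. **Arch measure.** Use one name and one definition in Table A2, section 2.4.2 and the entry criterion in section 2.2. Reconcile that definition with the threshold of 1.35; renaming the row on the form would not by itself settle this. Which measure and threshold are meant is for the investigators to state.
3. **Silfverskiold.** Give two labelled fields, knee extended and knee bent.

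The cost is a revision of the form and small edits to sections 2.4.2 and 2.2. The same footprint and ankle examination serve, so no procedure is added. If forms have already been filled in, the footprint indices can be recomputed where prints were kept, but an angle recorded without its knee position cannot be recovered. The third change is therefore the one that depends most on being made early.

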
### 2.5. Blinding and Monitoring

Participants and their parents/guardians will be blinded as to which group they are allocated to and will not see the other group.

An initial assessment will be made, these same measurements will be repeated 3 times throughout the duration of the study. In total we will obtain 4 measurements for statistical analysis.

The second measurement will be a month of treatment; in addition, in this visit we will assess the state of the FO and verify that the exercises are going well. We will ask about the FO, if any pain has appeared that was not there before, any blisters or reddened areas. In the event that the adaptation to the FO has not been good, we will make the necessary adjustments to the FO, such as lowering the MLA. If any subject needs their FO to be modified, they will be called by telephone after 2 weeks to see the evolution; in the event that it has not improved, it will be cited to re-evaluate the FO.

To corroborate that the execution of the exercises is good, we will ask the participant to repeat them, and in case there is an exercise that is not being performed correctly, we will explain it again.

The third assessment will be in the middle of the treatment/study period, that is, at 6 months. At this stage, all the initial measurements/assessments will be conducted again, as well as the last one at 12 months.

The estimated time for the measurement assessments is one hour for the 1st visit and 30 min for the rest of the visits.

